## Abstract

**Background:**

Adolescence presents a window of opportunity to establish good nutrition and physical activity behaviours to carry throughout the life course. Adolescents are at risk of developing cardiovascular and other chronic diseases due to poor the complex interplay of physical and mental health lifestyle risk factors. Text messaging is adolescents main form of everyday communication and text message programs offer a potential solution for support and improvement of lifestyle health behaviours. The primary aim of this study is to determine effectiveness of the Health4Me text message program to improve adolescent’s physical activity or nutrition behaviours among adolescents over 6-months, compared to usual care.

**Methods:**

Health4Me is a virtual, two-arm, single-blind randomised controlled trial, delivering a 6-month healthy lifestyle text message program with optional health counselling. Recruitment will be through digital advertising and primary care services. In total, 330 adolescents will be randomised 1:1 to intervention or control (usual care) groups. The intervention group will receive 4–5 text messages per week for 6-months. All text messages have been co-designed with adolescents. Messages promote a healthy lifestyle by providing practical information, health tips, motivation and support for behaviour change for physical activity, nutrition, mental health, body image, popular digital media and climate and planetary health. Virtual assessments will occur at baseline and 6-months assessing physical health (physical activity, nutrition, body mass index, sleep), mental health (quality of life, self-efficacy, psychological distress, anxiety, depression, eating disorder risk) and lifestyle outcomes (food insecurity and eHealth literacy).

**Discussion:**

This study will determine the effectiveness of a 6-month healthy lifestyle text message intervention to improve physical activity and nutrition outcomes in adolescents.

**Trial registration:**

Australia New Zealand Clinical Trials Registry (ANZCTR) ACTRN12622000949785, Date registered: 05/07/2022.

## Introduction

Adolescence presents a window of opportunity to establish good nutrition and physical activity behaviours, which are the pillars of overall future physical and mental health [1]. However, the current picture of adolescent physical and mental health worldwide is concerning. Research has established associations between several lifestyle risk factors, including physical activity, nutrition, sedentary behaviour and sleep that are contributing to the declining physical and mental health status of adolescents [2, 3]. Adolescents in high income countries, like Australia are not meeting national guidelines for these risk factors. National Australian data from 2017 to 18 and 2011–12 found 96% of adolescents do not meet national guidelines for fruit and vegetable intake [4], and 41% of their total energy intake came from discretionary foods [5], respectively. Globally more than 80% of adolescents are not engaged in sufficient physical activity [6]. Reducing sedentary behaviour is important for both physical and mental health. However, Australian data from 2017 to 18 found only 7.9% of 13–17-year olds met the physical activity guideline, and only 20% met the sedentary screen-based behaviour guideline [7]. Short sleep duration amongst adolescents is also prevalent. For example, in a sample of American students, 6 out of 10 middle school students and 7 out of 10 high school students were not sleeping for the recommended 8–10 hours per night [8]. The COVID-19 pandemic negatively impacted the lifestyle behaviours Australian adolescents. Cross-sectional data from a sample of 983 adolescents indicated increases of excessive recreational screen time (86 to 94%) and insufficient fruit intake (20 to 30%). As well, this data indicated proportions of adolescents engaging in insufficient physical activity (82%) and vegetable intake (84%) remained concerning [3]. The intersection of risk factors for both obesity and mental health demonstrates the need for holistic programs which provide support to improve lifestyle risk factors.

Systematic reviews have shown that poor nutrition, physical inactivity, sedentary behaviour and sleep are all linked to poor mental health [9–11] and to obesity [12, 13]. Globally, the presence of overweight and obesity among children and adolescents 5–19 years has risen from 4% in 1975 to over 18% in 2016 [14]. By 2030 it is predicted there will be 254 million children and adolescents with obesity [15]. National Australian data from 2017 to 18 found 25% of children and adolescents 2–17 years have overweight or obesity [16]. Similarly, the period of adolescence is the highest risk developmental stage for the onset of mental illness [17]. In adolescents it has been shown that there is a bi-directional association between overweight and obesity and poor mental health [18, 19]. Overweight and obesity during adolescence has immediate impacts on quality of life [20], which if not addressed may have long term consequences on wellbeing [21]. Research has also demonstrated significant links of unhealthy diets to mental health in adolescence [9, 22]. Adolescent mental health is of growing concern with 14% of 10–19-year-olds globally experiencing a mental disorder with depression, anxiety and behavioural disorders among the leading causes of illness and disability [1]. In Australia, 20% of adolescents aged 12–17 had high or very high levels of psychological distress and 14% experienced a mental disorder [23]. The COVID-19 pandemic has also significantly disrupted the lives of Australian adolescents, with research showing a worsening in mental health [24], with the potential for long-term impacts [25]. Failing to address mental health conditions in adolescence can harm physical and mental health and hinder leading a fulfilling life in adulthood [1], displaying a growing need for action in these areas.

The current approach to improving the health behaviours of adolescents needs to be aligned with best practice recommendations [26]. Programs that target mental health often do not focus on nutrition and physical activity behaviours [27] and programs with an obesity prevention or management lens can be stigmatizing [28]. There is a need to develop accessible and scalable programs which focus on prevention through management of lifestyle health behaviours and mindful of impacts on mental health. This is in line with the Australian National Obesity Strategy 2022–32 where young people recognised the need for holistic approaches to support a healthy lifestyle [29]. Recent research has shown that the primary care health setting in Australia is appropriate for delivering preventive care to adolescents [30]. However, the barriers to primary care services are bi-directional, adolescents cite barries including cost of visits, opening hours, transport to and from services, concerns about confidentiality and feeling embarrassed [31]. General practitioners (GPs) have indicated that time is a major barrier as adolescents often need longer consultations to build strong relationships and overcome communication barriers to deliver lifestyle health information [30]. Therefore, for prevention programs to be effective, these barriers must also be addressed so that adolescents are empowered to improve their lifestyle health behaviours.

The ubiquitous nature of mobile health (mHealth) programs offers a potential solution to address these risks. There is strong evidence supporting the efficacy of text messaging in adults for facilitating positive behaviour change for physical activity [32], nutrition [33], mental health [34] and management of cardiovascular disease risk [35]. A systematic review assessing text messaging as an intervention for adolescent physical activity and sedentary behaviour found that there was high heterogeneity of study design which prevented conclusions as to which intervention elements were linked to increased effectiveness, and therefore concluded that further research is needed with text messaging as the focus of the intervention to demonstrate the effect of text messages on these lifestyle health behaviours [36]. Text messaging is well suited to adolescents as 94% of adolescents in Australia own a mobile phone [37], text messaging is their main form of communication and direct communication can be made with participants for minimal cost. Text messaging also improves accessibility to programs from those in rural, remote, and disadvantaged populations who have inequitable access to healthcare and where the COVID-19 pandemic has only increased these inequities [38]. There is a need for simple and accessible solutions that focus on prevention, specifically targeting physical and mental health among adolescents.

The primary aim of this study is to determine, in a single blind randomized controlled trial (RCT), whether a semi-personalised text message healthy lifestyle program (Health4Me) compared to usual care will improve adolescents’ physical activity (moderate to vigorous physical activity [MVPA] minutes per day) or nutrition (vegetable intake > 3 serves per day) behaviours among adolescents over 6-months. Further, to determine if the text message program can improve or maintain other physical and mental health and lifestyle outcome, to explore the acceptability, utility and engagement with Health4Me among youth and inform implementation into primary health care services in Australia.

## Methods

### Study design

The Health4Me study is a virtual, randomised, controlled, single-blind trial, which delivers a 6-month text message healthy lifestyle program with optional health counselling to 330 healthy adolescents (12–18 years old inclusive) (Fig. 1).

**Fig. 1 Fig1:**
[figure not shown]
Flow chart of study design for Health4Me study

### Randomization and blinding

Participants will be randomly allocated to either the intervention or control group. The control group will receive usual care (no intervention). Participants will view digital advertisements for the study on social media, after clicking on a link it will take them to the participant information sheet which they can read and provide informed e-consent. After obtaining electronic consent from adolescents (and their parents or guardians if < 14 years old) and completing the baseline assessment on a secure web-based database, a member of the research team will randomize the participant via a centralized, computerized randomisation program in a uniform 1:1 allocation ratio (intervention: control). Randomization is based on both permuted blocks with randomized block sizes and stratification, where the strata are age and gender. A randomization list will be generated by an independent statistician. Members of the research team who enrol and conduct follow-ups with participants will be blinded to group allocation.

For each participant, the randomization program automatically produces a study identification number. On the following Monday after the baseline assessment, the computer system automatically sends the assigned text message program to the participant. Therefore, the random allocation sequence will be concealed from study personnel at baseline and at 6-months. Participants will be encouraged not to discuss whether they are or are not receiving the text messages until the end of the 6-month follow-up.

### Study population

As the study is virtual, there are no physical sites for recruitment. Rather, participants will be recruited through digital advertisements. GPs will also be informed of the study via email and encouraged to advertise this to their adolescent patients. A log of all recruitment strategies will be kept. Participants will be eligible to take part if they are: (1) 12–18 years old inclusive; (2) own a mobile phone capable of sending and receiving text messages; (3) have sufficient English to read text messages pitched at a 7th grade reading level; and (4) provide electronic consent (or from their parents or guardians if < 14 years old).

Participants will be excluded if they: (1) have a diagnosis of type 1 or type 2 diabetes mellitus; (2) have a previous or current diagnosis of an eating disorder or are at high risk for an eating disorder as assessed in screening; (3) weight < 25th centile for age; (4) have had recent rapid weight loss; (5) have a medical condition which would preclude providing informed consent or ability to comply with the study protocol; (6) are enrolled in an alternative randomised lifestyle management program; (7) are pregnant or planning to become pregnant during the 6-month intervention; and (8) are unable to read English at a 7th grade reading level. Screening will occur for eating disorders at baseline, 2, 4 and 6-months and any participant who scores above the pre-determined threshold will trigger the study team to refer appropriately. Both screening and recruitment logs will be kept by the research team for those participants who are ineligible or decline to participate, including reasons for non-participation.

### Control group

The control group will receive usual care. For this study, usual care is defined as accessing available information and health services to maintain a healthy lifestyle. Participants in the control group receive an initial text message welcoming them to the study, and one text message at 2, 4 and 6 months respectively. The messages at 2 and 4 months will have a link to complete the eating disorder screening and the message at 6 months will direct them to complete all follow-up assessments. Participants in the control group will be offered the text message intervention after the 6-month follow-up assessments are complete at no cost. However, they will not be able to receive health counselling.

### Intervention group

The intervention group will receive usual care, plus a 6-month text message support program with text messages focussed over six key priority areas for improving physical and mental health, namely nutrition, physical activity, mental health, body image, climate and planetary health and popular digital media (e.g., social media), as well as the option to speak with a university-trained health counsellor.

#### Message content

Message program content was developed according to a previously published model [39]. Briefly, an established youth advisory group (comprised of 16 adolescents aged 13 to 18 years old inclusive) identified current top health issues for young people [40] and assisted in drafting relevant and practical content, informed by national physical activity, dietary and sedentary screen-based behaviour guidelines, behaviour change theories and lived experience of being a young person in today’s world. Furthermore, text messages will also include information on how the primary care system works and how to connect with primary care services, including GPs. Included in the bank of text messages is one welcome message and one final text message. Each message will have a unique signature as the study name to ensure that participants know these messages are from the research study and participants at enrolment will be told how to unsubscribe if required.

#### Message frequency and sequence

Each intervention participant will receive a semipersonalized and customized set of text messages, sent on four random days per week and at random times. If the participant is attending high school, the weekday text messages will only be sent before or after school hours (8.00 AM to 9.00 AM or 3.30 PM to 7.30 PM). Each text message is unique and will only be sent once throughout the 6-month program. The messages are semipersonalized by including the participants name and selecting content relevant to their age and dietary behaviours (e.g., vegetarian). Participants can also update their key information, (e.g., change in dietary behaviours) through the course of the study and this will be reflected in the ongoing text messages they receive. Messages are sent at no cost to the participants and a bulk-rate cost to the study. However, if participants reply to the study team, these will be paid for by the participant at standard short message service (SMS) rates. The intervention will encourage two-way communication; however, it is for the participant to decide how much they engage with the study. All replies and responses are monitored by the health counsellor and responses given in 72 hours when required.

#### Health counsellor

Once a month (6 in total), intervention participants will be sent a text message encouraging them to call the university qualified health counsellor to ask questions or request additional information. The personalised health counselling calls will last 10–15 minutes and will be delivered according to standardized protocol. The university qualified health counsellor (allied health or public health professional) will monitor and respond to participants’ request for a call each month either via text message or phone call within 3 working days. Participants are allowed 6 health counselling calls in total over 6-months. The health counselling calls will allow participants to set behavioural goals, discuss barriers and enablers to behaviour change, and their overall progress. This part of the intervention is based on the evidence based TEXTBITES Study for obesity prevention in adolescents [41].

#### Text message management system

The text message management system has been used successfully in two randomised controlled trials (TEXTBITES and EMPOWER-SMS) [42, 43]. Pre-specified algorithms are put in place to ensure that the intervention group are the only ones who receive the Health4Me message program. Each week, messages are randomly selected from the text message bank by the software system such that a variety of messages are delivered each week from the four key priority areas. Both groups are sent a welcome message at the beginning of the study and a concluding message after 6-months. Participants are instructed in the welcome message to save the dedicated number that the text messages come from, so that they are not seen as spam. They are also given details on how to unsubscribe from the messages if required. All participants receive information on safe and acceptable times to read text messages (e.g. not to read messages while driving) and contact details of the research team in case of any issues. A member of the research team will manage a study mobile phone, and a record is kept of all incoming messages from participants and outgoing messages from the health counsellor. Analysis of incoming and outgoing messages will be performed at the end of the study, as part of the process evaluation. If a participant from either group wishes to withdraw from the study, they can at any time by replying ‘STOP’ to any of the messages or contacting the research team. If a reason for withdrawal is provided, it will be recorded in the enrolment log.

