### Statistical considerations

For the outcome of MVPA (minutes per day), 312 (156 per group) participants are needed to achieve 90% power to observe the mean difference of 14.8 (control: 42.55 and intervention: 57.36) with standard deviations (SD) of 21.45 for control and 37.79 for intervention and accounting for 30% dropout. A two-sided two-sample unequal-variance t-test was used. The Bonferroni adjusted significance level of 0.025 was used to account for two primary outcomes. To detect a difference in vegetable intake at 6-months, 390 (195 per group) participants will achieve 90% power to detect 13.37% difference in the proportion of appropriate vegetable consumption (control: 4.85% and intervention: 18.22%) and accounting for 30% dropout [61]. The two-sided Z-Test with unpooled variance was used with the significance level of the test is 0.025. Therefore, a sample size of 390 will allow the detection of the change in MVPA or vegetable intake.

All statistical analyses will follow a pre-specified statistical analysis plan guided by our team statistician. Analyses of the primary and secondary outcomes will be conducted according to the intention-to-treat principle. Continuous outcomes at 6-months will be analysed using analysis of covariance (ANCOVA), and categorical outcomes at 6-months will be analysed using log-binomial regression, adjusting for the outcome values at baseline. Planned subgroup analyses will investigate interactions between treatment and subgroups, including categories of age, socioeconomic status and ethnicity, to explore trends for scale up. All tests will be two-sided with a significance level of 0.05. Analyses of the two primary outcomes will be controlled for the family-wise error rate using Holm correction [62]. No multiplicity adjustments will be performed for secondary outcomes as they are exploratory analyses. The analyses will be performed using SAS (V9.4 SAS Institute Inc. Cary NC, USA).

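### Replying STOP is a route out of the study and is not separated from ending the texts, which risks loss of 6-month data that differs by arm

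*Protocol article*

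**What the plan says.** Text message management system gives the exit route for both groups: a participant who "wishes to withdraw from the study, they can at any time by replying ‘STOP’ to any of the messages". Contacting the research team is the alternative. A reason is logged only if the participant offers one. STOP is the only keyword that the article names.

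Unsubscribing is mentioned in two places. Message content says that "participants at enrolment will be told how to unsubscribe if required". Text message management system, describing the welcome message, says: "They are also given details on how to unsubscribe from the messages if required". Neither place says how unsubscribing is done, whether it differs from STOP, or what it means for follow-up.

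Exposure to messages differs by design. The Abstract (Methods) states: "The intervention group will receive 4–5 text messages per week for 6-months". Message frequency and sequence gives four days per week. Under Control group, controls "receive an initial text message welcoming them to the study, and one text message at 2, 4 and 6 months respectively", and "the message at 6 months will direct them to complete all follow-up assessments". Text message management system adds a concluding message for both groups, which may or may not be the same as the 6-month text.

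Statistical considerations states: "Analyses of the primary and secondary outcomes will be conducted according to the intention-to-treat principle". It plans ANCOVA and log-binomial regression of the 6-month values and allows for a single dropout figure of 30%, not split by arm.

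**The concern.** Ending the texts and leaving the trial are different decisions. The first is non-adherence, and such a participant should still be measured. The second ends data collection. If one reply can serve for both, an adolescent who has had enough of the messages may be recorded as withdrawn and not be asked for the 6-month survey or sent the second accelerometer.

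The occasions for such a reply come from the treatment itself, so any resulting loss would probably depend on arm. An intention-to-treat commitment keeps people in the arm to which they were randomised, but it does not supply outcomes that were never collected. A missing-data method in the analysis plan would have to rest on assumptions about them. Because reasons are logged only if offered, message fatigue may not be distinguishable afterwards from a real wish to leave the study.

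**Working it through.** **1. Opportunities to reply, by arm.** Six months is taken as 26 weeks.
- Intervention: 4 × 26 = 104 to 5 × 26 = 130 messages.
- Control: welcome, 2, 4 and 6 months = 4, or 5 if the concluding message is separate.
- Ratio: from 104/5 ≈ 21 to 130/4 ≈ 33.

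This counts chances to reply. It is not a rate of stopping.

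**2. The plan's own sample sizes** (two-sided alpha 0.025, 90% power, so z = 2.241 + 1.282 = 3.523 and z² ≈ 12.41).
- MVPA, SDs 21.45 and 37.79, difference 14.8. Normal approximation: (21.45² + 37.79²) × 12.41 / 14.8² ≈ 107. The unequal-variance t-test gives 109 per group, and 109/0.70 = 155.7, so 156. This matches the article.
- Vegetable intake, 4.85% against 18.22%, unpooled variance: (0.0485 × 0.9515 + 0.1822 × 0.8178) × 12.41 / 0.1337² = 135.5, so 136 per group, and 136/0.70 = 194.3, so 195. This matches the article.

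The inflation for dropout is correct, but it uses one rate for both arms.

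**3. Power if loss is greater in the intervention arm.** Control dropout is held at 30%, and the intervention rates above 30% are assumptions. The article gives both 390 and 330 as the total; that mismatch is a separate matter, so both are shown.

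| Intervention dropout | Vegetable, 195/arm | MVPA, 195/arm | Vegetable, 165/arm | MVPA, 165/arm |
|---|---|---|---|---|
| 30% | 90.2% | 95.7% | 84.4% | 91.9% |
| 35% | 88.4% | 94.6% | 82.1% | 90.2% |
| 40% | 86.2% | 93.1% | 79.5% | 88.1% |
| 45% | 83.5% | 91.2% | 76.4% | 85.6% |
| 50% | 80.3% | 88.8% | 72.8% | 82.5% |

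Each extra 5 points of loss in the intervention arm costs roughly 2 to 4 points of power for vegetable intake and 1 to 3 for MVPA.

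**4. Possible bias with no true effect.** Let a fraction f of the intervention arm stop and go unobserved, with no corresponding loss in control. All inputs here are assumed.
- MVPA: if stoppers average g min/day below those who stay, the stayers' mean exceeds the whole-arm mean by f × g. With f from 0.05 to 0.20 and g of 5 or 10, the range is 0.05 × 5 = 0.25 to 0.20 × 10 = 2.0 min/day, against a design difference of 14.8.
- Vegetable intake: if no stopper meets the guideline and the whole-arm proportion is 4.85%, the observed proportion is 4.85%/(1 − f), which is 5.1% at f = 0.05 and 6.1% at f = 0.20. The bias is 0.3 to 1.2 points, against a design difference of 13.37.

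If stoppers were instead the more active participants, the sign would reverse.

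**The case against.** The STOP sentence is conditional. It offers a way out to someone who wants to leave the study and does not say that a person who is merely tired of the texts is treated as withdrawn. Unsubscribing is mentioned separately, so the trial may already distinguish the two acts in its full protocol or participant information sheet. Missing-data handling may be in the analysis plan, which is not shown. Contact does not depend on text alone: accelerometers are mailed, and Process measures plans focus-group invitations by text, email or phone. All of this stands, and it limits the point to a risk.

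Several stronger readings are tempting but not supported:
- *That message-stoppers are lost to follow-up, and unequally.* No text says that unsubscribing means withdrawal, and no rate by arm is given.
- *That STOP blocks the 6-month invitation.* A text invitation to the 6-month assessments is documented for controls only; the route for the intervention arm is not stated.
- *That almost all controls would remain.* The 30% allowance covers both arms.
- *That the analysis is not intention-to-treat.* The article commits to that principle.
- *That the effect would be overstated by f/(1 − f)*, that is 5%, 11% or 25% at f = 0.05, 0.10 or 0.20. This compares an effect D in continuers with an intention-to-treat effect of (1 − f)D. It requires that every stopper gains nothing, is unobserved and otherwise resembles continuers, that control loss causes no bias, and that only complete cases are analysed. Under that model the bias is zero when there is no true effect.

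The objection does not remove the rule as written. The article fixes a reply to any message as a way out of the study, names no other keyword, and does not say that those who end the texts are still assessed. If unsubscribing is done by STOP, the two acts coincide. If it is done another way, someone who texts STOP only to end the messages still uses the withdrawal command. An analysis plan cannot recover outcomes that were not sought.

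**Conclusion.** The point holds as a weakness in a stated conduct rule, not as a demonstrated loss of data. The article does not separate ending the messages from leaving follow-up, and the occasions to send STOP differ by a factor of about 21 to 33 between arms. Arm-related missing 6-month outcomes are therefore a foreseeable risk for both co-primary outcomes.

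Its size and direction cannot be derived from the article. Under the assumed inputs above, the bias with no true effect is small against the design differences. The power cost is moderate: with 330 randomised, 40% rather than 30% loss in the intervention arm takes vegetable power from 84.4% to 79.5%. These figures are illustrations only. The rule should be changed because the change is cheap and outcomes that were never sought cannot be recovered later.

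**What to change.** State that a STOP or unsubscribe reply ends the programme messages only. State also that the 6-month survey and accelerometer data are still sought by a route outside the programme, such as email or phone, unless the participant explicitly withdraws from follow-up. Say what the reply does in the control arm, where the texts are study contacts and not programme content. Keep a simple, clearly described way to withdraw fully. Record the two events separately, by arm and with dates, and analyse message-stoppers as randomised.

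The cost is a wording change to the protocol and participant information, one status field in the database and a few extra contacts. The real downside is that some participants who replied STOP, many of them minors, will be contacted again. The participant information must therefore explain this beforehand, and the full-withdrawal route must be as easy to use as STOP.
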